## Assignment of interventions: blinding

### Who will be blinded {17a}

Owing to the nature of the intervention, participants and those providing the intervention will not be blinded, as group allocation will be evident to them. However, data collectors and the statistician will be blinded.

### Procedure for unblinding if needed {17b}

Not applicable. As this study involves an exercise intervention that is obvious to participants, a procedure for unblinding is not required.

## Data collection and management

### Plans for assessment and collection of outcomes {18a}

All participants will be assessed on all outcome measures at baseline (T0) and at re-evaluation (T2). Prior to data collection, data collectors will receive sufficient training on measurement methods, including the TMT-J, the digit span test, the Stroop and reverse-Stroop test and the single-leg stance time with eyes open and closed. Collected data will be recorded on a record sheet displaying written results, and any missing or inconsistent data will be checked and corrected as necessary. All data will be checked for completeness and accuracy before being entered into a secure electronic database. Before statistical analysis, all data will be cleaned, outliers will be examined, and the normality of the distribution will be tested.

### Plans to promote participant retention and complete follow-up {18b}

The participants who would be unavailable for assessment at the time of the re-evaluation (t2), or who have missing or anomalous data, will be contacted again and offered an opportunity for reassessment. Additionally, participants allocated to the control group will be provided the opportunity to experience the DTT after the completion of the study period.

### Data management {19}

A second investigator will cross-check, and the principal investigator will check again the entered data. A correspondence table linking anonymized IDs will be created and stored in a manner that prevents identification of individuals. When a participant is enrolled in the study, the informed consent form and end-of-trial date will be recorded in secure storage on the university server, and the signed paper forms will be stored in a locked room within the institution. All research data, including participants’ materials, will be archived within the institution. In accordance with institutional regulations, the data will be retained for 10 years after the final publication of study results.

### Confidentiality {27}

Personal data collected from the study participants will be handled in accordance with the Act on the Protection of Personal Information and the standards established by the institutional representative of the research institution. The principal investigator will take all necessary precautions to prevent the leakage, loss, or damage of personal data. Participants’ names written on the questionnaire will be removed during the data transcription and replaced with a research identification (ID) number. The research ID will be a non-identifiable number, beginning with 001.

### Plans for collection, laboratory evaluation and storage of biological specimens for genetic or molecular analysis in this trial/future use {33}

Not applicable. This study will not collect any biological specimens.

## Statistical methods

### Statistical methods for primary and secondary outcomes {20a}

For the primary analysis, the analysis of covariance (ANCOVA) will be performed to compare post-intervention scores between the two groups, with age, sex, and baseline values of each outcome included as covariates. For supplementary analyses, paired t-tests will be conducted to compare pre-intervention and post-intervention means within each group.

The above analyses will be applied to the primary outcomes (TMT-A, TMT-B, and ΔTMT) and secondary outcomes (the digit span test, the Stroop and reverse-Stroop test, and the single-leg stance time).

All analyses will be performed using SPSS Version 29.0 (IBM Corp., Armonk, NY, U.S.) and SAS version 9.4 (SAS Inc., Cary., NC, U.S.).

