### Trial design {8}

The study design is an RCT, in which the DTT is compared to a control group of participants who maintain their usual daily routine. The allocation ratio is 1:1. The superiority of DTT compared to the control group will be tested.

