### Primary outcome assessment

To evaluate attentional function, the TMT-J [26] will be used. TMT-J consists of Part A (TMT-A) and Part B (TMT-B). In TMT-A, circles numbered from 1 to 25 are presented, and participants were instructed to quickly connect numbers in ascending order by drawing lines. In Part B (TMT-B), the circles contained either numbers from 1 to 13 or the first 12 characters of the Japanese Hiragana alphabet. Participants are instructed to connect the numbers and characters in alternating order. The time required (in seconds) for each test will be measured and used as an outcome indicator. Additionally, ΔTMT will be calculated by subtracting the time for TMT-A from that for TMT-B (ΔTMT = TMT-B − TMT-A). TMT-A is used to assess sustained attention, while TMT-B is used to evaluate divided attention, with shorter completion times indicating better performance. Additionally, smaller ΔTMT values indicate better executive function. Errors made during the tests will be recorded and included in the analysis as appropriate.

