## Participant timeline {13}

### Sample size {14}

We calculated the required sample size as 60 participants based on the results of previous studies on TMT-A and TMT-B [16–18, 21]. We expected a 15-second difference in change scores (post–pre) between the two groups on the TMT-A, with a standard deviation (SD) of 15 seconds. This corresponds to an effect size of 1. Assuming a two-sided α of 0.05 and a statistical power (1–β) of 0.80, the required sample size is 34 participants (17 per group). Next, for TMT-B, we expected a 20-second difference in change scores (post–pre) between the two groups, with a SD of 25 seconds. This corresponds to an effect size of 0.8. Assuming a two-sided *α* of 0.05 and a statistical power (1–β) of 0.80, the required sample size is 52 participants (26 per group). Therefore, the final sample size was determined as 60 participants, considering the potential dropouts.

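### One superiority claim rests on three unranked primary outcomes, with no rule on which decides it; if any one suffices, the false-positive rate is roughly 9–12%

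*Protocol article*

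**What the plan says.** Under Trial design {8} there is one undivided claim: "The superiority of DTT compared to the control group will be tested".

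Under Statistical methods {20a}, "the analysis of covariance (ANCOVA) will be performed to compare post-intervention scores between the two groups", adjusted for age, sex and the outcome's own baseline. The section continues: "The above analyses will be applied to the primary outcomes (TMT-A, TMT-B, and ΔTMT) and secondary outcomes". The three primary outcomes get the same model, and none is put first.

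The third is computed from the other two: "ΔTMT = TMT-B − TMT-A" (Primary outcome assessment).

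Sample size {14} treats TMT-A and TMT-B separately. For TMT-A: "Assuming a two-sided α of 0.05 and a statistical power (1–β) of 0.80, the required sample size is 34 participants (17 per group"). For TMT-B it uses the same alpha and power and arrives at 52 participants (26 per group). The larger figure is then raised to 60 for dropout. ΔTMT has no expected effect, alpha or sample size.

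The article contains no ranking, no sharing of alpha, and no statement of how many primary outcomes must succeed. The Abstract speaks of a primary outcome in the singular, while {20a} lists three.

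**The concern.** A superiority trial needs a rule, fixed in advance, that turns its primary results into one conclusion. Here three tests feed one claim and the rule is absent. Two of the tests each receive the whole 5% in the sizing, and the third goes through the same analysis.

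Two things are at stake. The error rate of the main conclusion is undefined: it could be below 5% or about double that, depending on a rule nobody has written down. And the deciding outcome could be chosen after the results are known. The Background describes earlier findings on attention as inconsistent, so a trial meant to clarify them should not leave this open.

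**Working it through.** **Inputs from the protocol.** TMT-A: difference 15 s, SD 15 s, effect size 1. TMT-B: difference 20 s, SD 25 s, effect size 0.8. Two-sided α 0.05, power 0.80, allocation 1:1; 26 per group before dropout, 30 per group as planned. **Assumed:** the correlation r between TMT-A and TMT-B changes, which the protocol does not give; range 0 to 0.9.

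**1. The protocol's sample sizes.** The normal approximation n = 2(1.96 + 0.84)²/d² gives 16 per group for d = 1 and 25 for d = 0.8. The two-sample t-test (noncentral t) gives 17 and 26, as stated. So each calculation does use an unshared 0.05.

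**2. Dependence between the three tests.** Because ΔTMT = B − A,

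SD(Δ) = √(15² + 25² − 2·r·15·25) = √(850 − 750r)

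corr(A, Δ) = (25r − 15)/SD(Δ); corr(B, Δ) = (25 − 15r)/SD(Δ)

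At r = 0.5, SD(Δ) = √475 = 21.8 s and the correlations are −0.11 and 0.80. The independence figure 1 − 0.95³ = 14.3% is therefore too high.

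**3. Chance of at least one p < 0.05 under no effect** (2,000,000 simulated draws of the correlated statistics):

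| r | any of three | TMT-A or TMT-B only |
|---|---|---|
| 0 | 11.3% | 9.8% |
| 0.3 | 11.7% | 9.5% |
| 0.5 | 11.6% | 9.1% |
| 0.7 | 11.1% | 8.4% |
| 0.8 | 10.5% | 7.8% |
| 0.9 | 9.3% | 7.1% |

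Simulated ANCOVAs with the planned covariates, 26 per group, gave 11.3–12.0% for r from 0 to 0.7 (Monte Carlo error about 0.2 points).

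**4. If all three must be significant.** The error is below 5%. But the protocol's own effects imply a ΔTMT difference of 20 − 15 = 5 s. With SD(Δ) from 29.2 s (r = 0) to 15.8 s (r = 0.8), power for ΔTMT alone is 9–20% at 26 per group and 10–23% at 30. Power for all three cannot exceed that.

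**5. TMT-B power under possible remedies** (two-sample t-test, d = 0.8):

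| Alpha for TMT-B | 26 per group | 30 per group | n per group for 80% |
|---|---|---|---|
| 0.05 (single primary, or first in order) | 80.7% | 86.1% | 26 |
| 0.025 (split over two) | 71.6% | 78.5% | 31 |
| 0.0167 (split over three) | 65.8% | 73.5% | 35 |

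These figures allow for no gain in precision from baseline adjustment.

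**The case against.** The strongest reply is that the protocol nowhere says one significant outcome is enough. Sizing TMT-A and TMT-B separately and taking the larger number also fits a rule under which both must succeed. That rule does not inflate the error, and its power is not hopeless: at least 94.2 + 80.7 − 100 = 74.9% at 26 per group and 96.8 + 86.1 − 100 = 82.9% at 30. This stands in part. The text is open rather than wrong in one direction, but that reading leaves ΔTMT, also named primary, with no role.

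A reader might infer that the trial simply carries a 12% false-positive rate because each of three outcomes is tested at 0.05. The document does not support that. Any-one-wins is a reading it allows, not one it states. The 0.05 is explicit only for TMT-A and TMT-B; for ΔTMT it is inferred from the shared analysis. And 12% is the top of a range that depends on an unstated correlation.

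Multiplicity rules are often left to an analysis plan, and a fuller protocol exists. But this article already fixes three unranked primary outcomes and spends the full alpha twice in sizing. A later alpha split would contradict that sizing: TMT-B would fall below 80% power even with all 60 participants completing, before any gain from covariates.

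Finally, putting TMT-B first is a choice. Eligibility is built on TMT-A, and the three measures are assigned to different functions. Another order fixed in advance would control the error equally well.

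**Conclusion.** The point holds as a missing decision rule for a design that the protocol has otherwise fixed. If any one outcome suffices, the false-positive rate of the superiority claim is roughly 9–12%, or about 7–10% counting only the two outcomes with a stated alpha. Both ranges rest on the protocol's SDs and an assumed correlation of 0 to 0.9; the first also assumes that ΔTMT is tested at 0.05. If all three must succeed, the error is below 5%, but the sample size does not provide for that rule. The present sizing suits a single deciding outcome or a fixed order much better than an alpha split.

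**What to change.** Before anyone sees outcome data by group, state in Outcomes {12} and Statistical methods {20a} either one deciding primary outcome or a fixed test order, each step at two-sided 0.05. The order best supported by the sample size is:

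- TMT-B first, since it sets the 52 participants; superiority is concluded on TMT-B.
- TMT-A tested at 0.05 only if TMT-B is significant.
- ΔTMT moved to the secondary outcomes.

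This adds no participants and leaves TMT-B power as planned. The price is that TMT-A cannot be claimed alone if TMT-B fails. It is also more than an edit of wording. Trial status says recruitment began in August 2025, so the change needs a dated amendment with ethics approval and a registry update, as the section on protocol amendments {25} provides.

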### Interim analyses {21b}

Not applicable. This study involves a 4-week exercise intervention, and therefore interim analyses were deemed unnecessary.

### Methods for additional analyses (e.g., subgroup analyses) {20b}

Not applicable.

### Methods in analysis to handle protocol non-adherence and any statistical methods to handle missing data {20c}

The primary analysis of the outcome will be conducted using the intention-to-treat principle. Secondary analyses will be performed using the full analysis set and the per-protocol set. Multiple imputations will be conducted for missing values, which will be substituted with the most likely scores using the multiple imputation procedure, resulting in the creation of 10 output datasets.

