### Outcomes {12}

The following outcomes will be assessed at two time points, t0 and t2, as shown in Table 2, and differences in the change scores between the groups will be analyzed.

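### Ten imputations are too few for a repeatable p-value: at the implied dropout, the random seed can put a near-threshold primary result on either side of 0.05

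*Protocol article*

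**What the plan says.** Section {20c} of the protocol article gives the analysis principle: "The primary analysis of the outcome will be conducted using the intention-to-treat principle". It then gives the missing-data method: "Multiple imputations will be conducted for missing values, which will be substituted with the most likely scores using the multiple imputation procedure". The same sentence goes on to fix the number of imputations: "resulting in the creation of 10 output datasets". It does not say in so many words which analysis uses the imputed data. The sentence covers missing values in general and follows directly on the analysis sets, so the primary analysis is the natural reading.

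Three other sections bear on the point:

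- **Statistical methods {20a}:** the primary model is an ANCOVA of the post-intervention score with age, sex and the baseline value as covariates. It is applied to TMT-A, TMT-B and ΔTMT as primary outcomes.
- **Outcomes {12}:** "The following outcomes will be assessed at two time points, t0 and t2". There is no intermediate measurement.
- **Sample size {14}:** after a requirement of 52 for TMT-B, "the final sample size was determined as 60 participants, considering the potential dropouts".

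**The concern.** Multiple imputation fills each gap with random draws, so the pooled estimate and p-value depend partly on the seed. That dependence shrinks as the number of imputations m grows. A small m is often defended on efficiency, but efficiency concerns the precision of the estimate. It does not say whether a p-value compared with 0.05 comes out the same when the analysis is rerun.

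The design gives imputation little to work with. A participant who misses t2 altogether has no post-baseline score. If the imputation model holds only the ANCOVA covariates, it targets essentially the same answer as the complete-case ANCOVA, and a small m mainly adds simulation noise. At stake is whether two correct runs of the stated plan on the same data could report different conclusions for a primary outcome.

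**Working it through.** **1. The plan's own figures.** Section {14} assumes the following: "We expected a 15-second difference in change scores (post–pre) between the two groups on the TMT-A, with a standard deviation (SD) of 15 seconds"; for TMT-B, "we expected a 20-second difference in change scores (post–pre) between the two groups, with a SD of 25 seconds". The standardised effects are 15/15 = 1.0 and 20/25 = 0.8. With two-sided α 0.05 and power 0.80, the two-sample t-test needs 16.7 and 25.5 per arm. Rounded up these are 17 and 26, or 34 and 52 in total, as the article states.

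**2. Implied missingness.** 60 − 52 = 8, and 8/60 = 13.3%. This is derived; the article gives no rate.

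**3. Analytic size of the seed noise.** Let B be the between-imputation variance and T = W + (1 + 1/m)B the total variance, where W is the within-imputation variance. The Monte Carlo variance of the pooled estimate is B/m. The fraction of missing information is FMI ≈ (1 + 1/m)B/T. Hence

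Monte Carlo SD / standard error ≈ √(FMI/(m + 1)).

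- With FMI set to the missing fraction 0.133 and m = 10: √(0.133/11) = 0.11.
- With the simulated FMI of about 0.15 and m = 10: √(0.15/11) = 0.12.
- With FMI 0.15 and m = 100: √(0.15/101) = 0.04.

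The relative efficiency at m = 10 is 1/(1 + 0.15/10) = 98.5%.

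**4. Simulation.** The set-up was 60 participants, 1:1, 8 outcomes missing completely at random, and proper normal imputation from arm, age, sex and baseline. Results were pooled by Rubin's rules with Barnard-Rubin degrees of freedom, using 4000 seeds per dataset and averaging over 40 datasets. Assumptions not in the article are a baseline-to-post correlation of 0.6 and no auxiliary variables. Each dataset was shifted to a chosen complete-case p. Ranges are the central 95% across seeds.

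With m = 10 and 8 of 60 missing:

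| Complete-case p | Seed range of p | Seeds with p above 0.05 |
|---|---|---|
| 0.005 | 0.002–0.016 | about 0% |
| 0.01 | 0.005–0.028 | 0.08% |
| 0.02 | 0.010–0.047 | 1.8% |
| 0.03 | 0.016–0.065 | 11% |
| 0.04 | 0.022–0.082 | 32% |

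With complete-case p = 0.03 and 8 of 60 missing:

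| m | Seed range of p | Seeds with p above 0.05 |
|---|---|---|
| 10 | 0.016–0.065 | 11% |
| 20 | 0.019–0.052 | 3.7% |
| 50 | 0.023–0.043 | 0.3% |
| 100 | 0.025–0.039 | 0.01% |

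At complete-case p = 0.04 the share above 0.05 falls from 32% at m = 10 to 4.4% at m = 100. More imputations shrink the problem but do not abolish it very close to the threshold.

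**5. Other amounts of missing data, m = 10.** With 6 missing, 7% of seeds exceed 0.05 at complete-case p = 0.03, and 0.01% at p = 0.01. With 12 missing, the figures are 21% and 0.7%.

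**6. How often it would matter.** The treatment effect was set at 0.64 outcome SDs. With a correlation of 0.6 the residual SD is √(1 − 0.6²) = 0.8, so this is 0.64/0.8 = 0.8 residual SDs, the plan's TMT-B effect size. Simulated power was about 77%. Two seeds disagreed about p < 0.05 in 5.2% of trials at m = 10, 2.4% at m = 50 and 1.5% at m = 100. With no treatment effect, the rejection rate was 4.8% at m = 10 and 4.9% at m = 100.

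**The case against.** The case for leaving the plan alone has substance.

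- **It rarely matters.** The disagreement rate is about 5% for TMT-B at the planned effect. A rough normal approximation gives about 2% for TMT-A. Efficiency is 98.5%, and Rubin's rules already include a term for finite m, so neither bias nor loss of type I error control is shown. This stands, and it limits the point to a minor one.
- **Missingness may be lower.** Section {18b} offers reassessment to those who miss t2 or have missing data. Section {11c} ties the control group's payment to completing the post-intervention evaluation. The 13% is an implied allowance, not a forecast. This also stands. With 6 missing, however, 7% of seeds still exceed 0.05 at complete-case p = 0.03.
- **The imputation model is not stated.** Other baseline scores could enter it. A participant lacking one t2 test may have the others, and those scores would reduce the noise. This stands as a limit on the simulated figures, which describe loss of the whole visit and no auxiliary variables.
- **A seed may be fixed elsewhere.** The full protocol or analysis plan may set it, and section {31c} makes the statistical code available on request. The absence of a seed from the article is therefore not an error. A fixed seed makes the reported run repeatable, but the result still depends on which seed was chosen. Only a larger m reduces that dependence.

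The objection does not remove the number itself. Ten is written in this article, so it is not a detail left to an unseen document.

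**Conclusion.** The point holds as a minor reproducibility weakness. With 10 imputations and 8 of 60 outcomes missing, the seed-to-seed SD of the estimate is about 0.12 standard errors. A primary result with a complete-case p of about 0.02 to 0.05 can fall on either side of 0.05, and the risk rises steeply towards the threshold. The figures rest on the implied 13% loss, whole-visit missingness completely at random, an imputation model limited to arm, age, sex and baseline, and a correlation of 0.6. They also read {20c} as ordinary multiple imputation with random draws, applied to the primary analysis.

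A reader might infer that the seed could turn a clearly significant result into a non-significant one. The figures do not support that: at complete-case p = 0.01, fewer than 1 seed in 1000 gives p above 0.05. When 200 seeds were tried per trial at the TMT-B effect with m = 10, about 8% of trials had at least one p below 0.01 and at least one above 0.05. Those are the extremes of a long search, not what two ordinary runs would show. Nor does anything here suggest a biased estimate or an inflated type I error.

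**What to change.** In section {20c}, replace the figure of 10 datasets with at least 100 imputed datasets, and state that the random seed is set before the outcome data are analysed. The complete-case ANCOVA may be reported alongside as an optional check. With whole-visit loss and no auxiliary variables the two should nearly agree.

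The change should be made before analysis, because raising m after seeing a borderline p-value would look like selection. It takes one sentence and seconds of computing in SPSS or SAS. It needs no extra participants, visits or staff, and has no statistical drawback.

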### Plans to give access to the full protocol, participant level-data and statistical code {31c}

Sharing the participant-level dataset has not been planned. When the primary outcome results are published, the full protocol will also be submitted. However, the datasets analyzed during the current study, the statistical code, and the full protocol will be available from the corresponding author on reasonable request. In such cases, the access of data by a third party will likely require further approval from the ethics committee.

## Oversight and monitoring

### Composition of the coordinating centre and trial steering committee {5d}

This is a single-centre study designed, implemented, and coordinated at Fukushima Medical University. Day-to-day support for the trial is provided by the following staff:Principal investigator: Supervises the trial, conducts trial registration and participant enrolment, obtains informed consent, and ensures that the follow-up is conducted in accordance with the protocol.Data manager: Organizes data acquisition and safeguards the quality of the data.Data collectors: Conduct data acquisition, including assessments of attention and balance functions.Statistician: analyzes data after trial completion.

The principal investigator, data manager, data collectors, and statistician will meet before, during, and after the trial.

In this study, no formal independent committees, such as a steering committee or a data monitoring committee, will be established owing to the fact that it is a single-centre study with a low-risk, non-invasive intervention.

